# Revascularization with BYCROSS atherectomy device- protocol of a prospective multicenter observational study

**DOI:** 10.1186/s42155-023-00404-8

**Published:** 2023-12-05

**Keywords:** Critical limb ischemia, Endovascular revascularization, Mechanical thrombectomy, Thromboaspiration, Limb salvage, Crossing the occlusion device, Bi-directional rotational atherectomy, BYCROSS™ atherectomy device

## Abstract

**Background:**

The BYCROSS™ device is a novel device intended for use in atherectomy of the peripheral arterial disease (PAD). With the BYCROSS™ atherectomy system, also prolonged calcifying lesions can be treated in a minimally invasive manner, which was previously reserved for bypass surgery. The aim of this study is to collect additional clinical data on safety and performance of the BYCROSS™ from patients undergoing revascularization of severely stenotic or occluded peripheral arterial vessels with the BYCROSS™.

**Methods and design:**

This is an investigator-initiated national prospective multicenter observational study in patients with PAD. Sixty patients (20 per center) with PAD with stenosis higher than 80% or complete occlusion (de novo or recurrent stenosis) of vessels below the aortic bifurcation (min 3 mm vessel diameter) will be recruited. Three vascular surgery centers are participating in the study. The primary efficacy endpoint is procedural success, defined as passage of the occlusion through the BYCROSS device, and safety outcomes, explicated as freedom from device-related serious adverse events (SADEs). Secondary endpoints include primary and secondary patency rates, change in Rutherford classification, and freedom from amputation at 3 and 12 months.

**Discussion:**

The BYCROSS atherectomy system may be a novel device for the minimally invasive treatment of prolonged calcified lesions previously reserved for bypass surgery. This national prospective multicenter observational study could represent another step in demonstrating the efficancy and safety of this device for treatment of PAD.

**Trial registration:**

#DRKS00029947 (who.int).

**Protocol approval id:**

#22–0047(Ethics Committee at Ludwig-Maximilians-University Munich).

## Background

Approximately 230 million people are affected by vascular occlusive disease [1] worldwide. Overall, the incidence of PAD has steadily increased in recent years. As a result, the proportion of symptomatic patients requiring treatment is also increasing [2]. The focus has been on endovascular therapy as "first-line" therapy [3]. The BEST-CLI Trial could change the perspective. The results showed bypass surgery (even if an adequate great saphenous vein (GSV) is present) could provide better outcomes compared with endovascular treatment. The incidence for death or major adverse limb event (MALE) was significant lower in the bypass group with adequate GSV [4]. In contrast to the BEST-CLI trial, the BASIL-2 trial showed that endovascular treatment was associated with better outcomes (reduction in MALE) compared with bypass (vein). At the BEST-CLI Trial newer endovascular techniques, such as atherectomy, were not specifically mentioned and included in the comparison.

In addition to classical balloon angioplasty [5, 6], atherectomy is a procedure for the treatment of complex and persistent lesions [7, 8]. This method has been used for a variety of occlusive procedures [9, 10]. Despite the widespread use of these therapies, there is still considerable room for improvement as each available atherectomy system has its own limitations. (for example, in very long calcified lesions, complete occlusions, or the diameter of the created canal) [11]. In addition, atherectomy is associated with certain risks such as distal embolism, vascular injuries as well as perforation.

The innovative BYCROSS™ atherectomy system (TARYAG-MEDICAL GmbH, [name]; Fig. 1) used in this study, represents a further development of existing atherectomy systems. During development, several limitations encountered in other systems were identified and eliminated.

**Fig. 1 Fig1:**
[figure not shown]
Special features of the ByCross® system: The system is advanced into the target vessel in a 6-French sheath (**a**) attached to the handle, through which the suction pump housed in the handle simultaneously with the porous shaft below the tip (**b**), which follows the principle of the Archimedean screw, aspirates and transports debris. The catheter tip has a variable diameter. This measures between 1.9 mm (**b**) and 4.7 mm (**c**) with the nitinol cutting wire extended. **d** Overview of Bycross atherectomy device, (Courtesy of Taryag Medical Inc., Israel

## Methods

### Study aim

The aim of this prospective national multicenter observational study is to collect further clinical data on the safety and performance of the BYCROSS™ atherectomy system and to monitor treatment success after one year.

In the future, promising catheter-based treatments using the Bycross System could be made available to more patients. This could eliminate many more invasive procedures (e.g., bypass surgery), thereby increasing patient safety.

### Ethics

The study is being conducted in accordance with the Declaration of Helsinki on Research Involving Human Subjects and in compliance with the ICH Principles of Good Clinical Practice and additional local guidelines. This study was reviewed and approved by the Ethics Committee at Ludwig-Maximilians-University Munich, project-nr: 22–0047.

### Study design

The study is designed as a multicenter (3 centers), prospective, single arm, observational study. The success of the procedure (primary endpoint) will be assessed in each participating subject, as well as safety outcomes (defined as freedom from serious adverse events associated with the device (SADE)). A total of 60 (target 20 each center) subjects with a symptomatic PAD will be enrolled in the study. After written informed consent, subjects will be continuously enrolled (registered). Subjects will be followed for a period of 12 months, including follow-up after, and follow-up 90 days after the procedure. The detailed study procedures are shown in the flowchart of study activities (Fig. 2).

**Fig. 2 Fig2:**
[figure not shown]
Study Activity Flow Chart. ^1^*SAE* Serious adverse event, ^2^*ABI* Ankle-Brachial-Index, ^3^Rutherford scale [12]; ^4^*FU* Follow-up

### Inclusion and Exclusion criteria

Table 1 shows the inclusion and exclusion criteria.

**Table 1 Tab1:** Overview of Inclusion and exclusion criteria

Inclusion criteria
a. Age ≥ 18
b. Subject has documented symptomatic chronic peripheral vascular disease at a vessel below the aortic bifurcation
c. Severely stenotic occlusion target vessel (stenosis ≥ 80%)
d. Subject has been informed on the nature of the study and has provided informed consent
e. Subject is capable of meeting study requirements including presences at follow-up visits
Exclusion criteria
a. Vessels of the cardiopulmonary, coronary or cerebral circulations
b. Undersized vessel diameters (< 3 mm)
c. Perforation of the vessel distally or proximally to the occlusion segment prior atherectomy
d. Subintimal position of the guiding catheter or the guidewire
e. Use in stents or stent grafts if the guidewire has become threaded at any point in the wire mesh of stent or stent graft or the lining of the stent graft
f. Target is at vessel segment which includes tortuous course with radius of curvature < = 40 mm
g. Access pathway includes tortuous course with radius of curvature < = 25 mm, in specific extremely sharp aortic bifurcation
h. In aneurysmatically altered iliac vessel segments
i. If the introducer sheath, the guide catheter, the guidewire or the BYCROSS™ sustains any visible damage, especially kinking
j. In the fracture areas of broken stents
k. Known or suspected allergy to any of the components of the system or to a medicinal product to be administered in connection with the planned procedure
l. Persistent vasospasm
m. Patient is pregnant

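### Table 1 lists procedural events, including damage to the BYCROSS itself, as exclusion criteria for subjects who are already registered

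*Protocol article*

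**What the plan says.** The Study design section sets the order of events: "After written informed consent, subjects will be continuously enrolled (registered". The Study procedure section puts screening before the procedure. The planned size is fixed in the same place: "A total of 60 (target 20 each center) subjects with a symptomatic PAD will be enrolled in the study". The analysed group is described only in general terms: "The success of the procedure (primary endpoint) will be assessed in each participating subject, as well as safety outcomes".

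Table 1, under exclusion criteria, includes:

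- Criterion i, on the state of the equipment: "If the introducer sheath, the guide catheter, the guidewire or the BYCROSS™ sustains any visible damage, especially kinking"
- Criterion d, on where the instruments lie: "Subintimal position of the guiding catheter or the guidewire"
- Criterion l, with no time point: "Persistent vasospasm"
- Criterion c, on injury before the device is used: "Perforation of the vessel distally or proximally to the occlusion segment prior atherectomy"
- Criterion e, on previously stented segments, which applies "if the guidewire has become threaded at any point in the wire mesh of stent or stent graft"

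The Endpoints section defines the primary performance endpoint by passage of the occlusion with the BYCROSS and by residual stenosis. It defines the primary safety endpoint as freedom from device-related serious adverse events up to 90 days.

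**The concern.** An eligibility criterion should be decidable when the subject enters the study. Criteria d and e require a wire or catheter already in the vessel, and criterion i describes something that happens to the equipment. If they are used as study exclusions, they act on people who are already registered, and they act because of how the procedure is going.

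Criterion i matters most. The stated aim is to collect data on the safety and performance of the BYCROSS, and a device that kinks or is damaged in use bears directly on performance. As the table stands, that event is a reason for the subject not to be in the study. In a single-arm study no comparator group would share the distortion, so the reported success rate would carry all of it.

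**Working it through.** **When each criterion can be known**

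| Criterion | Earliest time it can be judged | After registration? |
|---|---|---|
| d, subintimal position | catheter or wire in the vessel | yes |
| e, wire threaded in stent | wire in the vessel | yes |
| i, visible damage | preparation or use of the equipment | in practice yes |
| c, perforation | any time up to atherectomy | possibly |
| l, vasospasm | no time given | possibly |

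So d and e are strictly procedural and i is so in practice. For c and l the text leaves both readings open.

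**The article's own figures.** The sample size is 3 centers × 20 = 60, with no statistical derivation to reproduce. The Discussion reports 39 of 42 successes in the earlier clinical investigation: 39/42 = 92.9% (exact 95% CI 80.5 to 98.5), which agrees with the stated rate of over 92%.

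**Effect on the success rate.** Let N = 60 be the number registered, s the number of successes and k the number of failures excluded during the procedure. The rate over all registered is s/N. The rate after exclusion is s/(N − k), which exceeds s/N whenever k > 0 and s > 0. The next exclusion adds s/[(N − k)(N − k − 1)].

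The earlier rate serves only as an anchor: 0.929 × 60 = 55.7, so take s = 56. The value of k is not in the document and is varied.

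| k | Rate | Exact (Clopper-Pearson) 95% CI |
|---|---|---|
| 0 | 56/60 = 93.3% | 83.8 to 98.2 |
| 1 | 56/59 = 94.9% | 85.9 to 98.9 |
| 2 | 56/58 = 96.6% | 88.1 to 99.6 |
| 3 | 56/57 = 98.2% | 90.6 to 99.96 |
| 4 | 56/56 = 100% | 93.6 to 100 |

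The steps are 56/(60 × 59) = 1.58 points, then 1.64, 1.69 and 1.75. With s = 54 (90.0%) they run from 54/(60 × 59) = 1.53 to 54/(55 × 54) = 1.82. Hence about 1.5 to 1.8 points per excluded failure at success rates of 90% or more.

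**Check on direction.** The upward shift applies to excluded failures. If an excluded subject would have been a success, for example after a damaged wire was exchanged, the rate falls slightly: 55/59 = 93.2% against 93.3%. One lost success costs about 0.1 point, and one lost failure adds about 1.6.

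**The case against.** **No removal rule is stated.** The article nowhere says that a registered subject who meets one of these criteria is withdrawn, dropped from analysis or replaced. The Study design section has success and safety assessed in participating subjects, which could be read as keeping them. The full protocol, the SAP or the two flow figures that are not shown may settle the matter. This stands in part: removal follows from applying Table 1 and is not a declared analysis rule. It does not remove the point, because an excluded subject can equally be read as no longer participating. An analysis set defined elsewhere would still conflict with an eligibility table that depends on procedural events.

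**Early events are not clearly device failures.** Criterion c is limited by its own words to the time before atherectomy, and d and e may also precede activation of the BYCROSS. Such cases may be non-attempts, and whether they belong in the denominator is a choice of estimand. This stands. Only i, and possibly l, supports the statement that device failures would be excluded.

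**Stronger readings that the article does not support:**

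- *Replacement.* A reader might suppose that 3 to 6 excluded subjects are replaced to reach 60. A reported 56/60 = 93.3% would then stand for 56/63 = 88.9% or 56/66 = 84.8%, an overstatement of about 4 to 8.5 points. No replacement is stated, and these counts are invented.
- *Secondary endpoint g (BYCROSS without primary wire passage).* A reader might infer that criterion d filters wire-first cases only. The Technique section says the device is still inserted via a guidewire, and d makes no exemption. At most, exposure to d may differ.
- *Secondary endpoint i (calcification and complications).* A reader might infer that this endpoint loses its events. Perforation during or after atherectomy is not excluded by c, and embolization and revision in Table 3 are not exclusions.
- *Safety.* A reader might infer that adverse events would go unrecorded. The Safety section requires serious events during the study to be documented and reported, with no exception for subjects who meet a Table 1 criterion. What stays open is whether such subjects count in the safety denominator.

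**Conclusion.** The point holds in a limited form. Table 1 states as subject exclusions three conditions (d, e and in practice i) that cannot be known before registration, and two more (c and l) that may first appear during the procedure. Applied as written, they make inclusion depend on procedural events, and criterion i makes it depend on failure of the device under study. This is a fault in a stated rule and not merely an omitted detail.

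The effect of dropping failures is always in the device's favour: about 1.5 to 1.8 points each with 60 subjects and a success rate of at least 90%. The total depends on how many are dropped, which the document does not give. The move from 93.3% to 98.2% rests on assuming 56 successes in 60 and three excluded failures; it is an illustration and not an estimate.

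**What to change.** Leave the device-use conditions exactly as they are, but move d, e and i out of study eligibility, and c and l as well when first seen during the procedure. Record each as a procedural event.

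Report both primary endpoints over all registered subjects in whom the procedure was started with BYCROSS intended, without replacement. Count damage to the BYCROSS in use as a performance failure. Show in the participant flow how many subjects did not receive the device and why. Give the device-activated subset as a sensitivity analysis, so that non-attempts under c, d and e are visible and a reader can see how much the choice of denominator matters.

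The cost is a revision of Table 1, a statement of the analysis set and a slightly less favourable success rate. No new measurements are needed. By the Trial status section, recruitment began in August 2022 and was expected to finish in December 2023, so the change would act mainly on analysis and reporting. Any registered subject already set aside under these criteria would have to be identified from site records and put back into the denominator.

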#### Study procedure

Schedule of events for this study are shown in Fig. 3. The study duration for each subject will be approximately 12 months, as follows:Screening of individuals who meet the inclusion criteriaProcedure with BYCROSS™ atherectomy systemFollow-up at 90 days after procedureFollow-up at 12 months after-procedure

**Fig. 3 Fig3:**
[figure not shown]
Participant flow through study

### Endpoints

The primary performance endpoint is technical success: Passage of the occlusion through the BYCROSS® device and residual stenosis after atherectomy of ≤ 50% compared to the reference diameter to allow angioplasty and/or stenting if needed, and complete procedural success with residual stenosis of ≤ 30%. The angiographic data will be examine at each study center by an independent radiologist or vascular surgeon with experience in interventional procedures. The primary safety endpoint is Freedom from device related Serious Adverse Events (SADEs) defined by the investigational site as part of normal reporting practices in any period between the procedure and 90 days after the procedure.

Secondary endpoints are listed in Table 2

**Table 2 Tab2:** Secondary endpoints, ^1^PACCS, peripheral arterial calcium scoring system

Secondary endpoints
a. target vessel revascularization (TVR) at 3 and 12 months
b. target lesion revascularization (TLR) at 3 and 12 months
c. The change of the Rutherford classification [13] at 3 and 12 months compared to pre-procedure
d. freedom from any minor or major amputation at 3 and 12 months
e. therapy success of the recanalization of the iliaco-femoro-popliteal vascular flow path depending on the access (crossover/antegrade/retrograde)
f. evaluation of the recanalization result of superficial femoralis artery (SFA) stenosis/occlusions using IVUS vs. angiography for the purpose of deciding on therapy for additional Angioplasty/stent implementation/Drug Eluting Balloon (DEB)
g. the evaluation of the recanalization result of BYCROSS use without primary wire passage
h. the evaluation of the recanalization result of stenoses/occlusions in combination with hybrid interventions
i. the evaluation of the correlation between calcification (measeared and calcified in accordance with PACCS^1 ^[14] and procedural complications

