### Follow-up

All participants will be followed-up after successful intervention. Clinical assessments will be performed 90 days (± 14 days) and 12 months (± 2 weeks) after the procedure. The following assessments and/or procedures will be collected and reported for all subjects at follow-up visit.Stenosis assessment by Duplex UltrasoundAnkle-Brachial-Index (ABI) measurement, depending on the ABI a treadmill test orTranscutaneous oxygen partial pressure measurement (TcPO2)Rutherford classification [13]Target vessel revascularization (TVR)Target lesion revascularization (TLR)Measurement Quality of Live via EQ5D [15] questionnaireMeasurement of pain via numeric pain scale (NRS) [16]Minor or Major Amputation neededSerious adverse events recording. Each event will be assessed whether root-cause for the event is related to device, procedure or not related.

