### Safety

Serious adverse events (SAEs) occurring during the conduct of this study must be documented. The list of potential SAEs is provided in Table 3. All SAEs and serious adverse device events (SADEs) associated with the device will be recorded at each follow-up visit. Reporting will be in accordance with local requirements and policies. If the investigator identifies an SAE/SADE, an SAE reporting form must be completed and faxed or emailed to Taryag Medical (TARYAG-MEDICAL GmbH, Israel, [contact]) within 24 h of the investigator’s knowledge of the event.

**Table 3 Tab3:** List of serious adverse events

Serious adverse events
a death
b serious deterioration in the health of the subject, that resulted in any of the following:
(I) life-threatening illness or injury,
(II) permanent impairment of a body structure or a body function,
(III) hospitalization or prolongation of patient hospitalization,
(IV) medical or surgical intervention to prevent life-threatening illness or injury or permanent impairment to a body structure or a body function,
(V) chronic disease
c Acute limb ischemia as a result of the procedure e.g. peripheral embolization
d Necessary thrombectomy/revision as a result of the procedure (surgical or interventional)
e Unplanned major amputation, above or below the knee

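### The primary safety endpoint counts only events the site labels device-related, so procedure-labelled embolization or revision can drop out of it; a broader rate should be reported beside it.

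*Protocol article*

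**What the plan says.** **Endpoint.** The Endpoints section defines primary safety as "Freedom from device related Serious Adverse Events (SADEs) defined by the investigational site as part of normal reporting practices", counted "in any period between the procedure and 90 days after the procedure". The Study design section and the abstract carry the same restriction to device-related events.

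**Causality.** Under Follow-up: "Each event will be assessed whether root-cause for the event is related to device, procedure or not related". *Procedure* is thus a label of its own, next to *device*.

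**Serious events.** Table 3 in the Safety section lists serious adverse events for the whole study. Item c reads "Acute limb ischemia as a result of the procedure e.g. peripheral embolization". Item d uses the same causal phrase for a thrombectomy or revision. The section also states: "All SAEs and serious adverse device events (SADEs) associated with the device will be recorded at each follow-up visit". Reporting follows local requirements.

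**Known harms.** The Background says that "atherectomy is associated with certain risks such as distal embolism, vascular injuries as well as perforation".

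**Other endpoints.** Table 2 includes target vessel and target lesion revascularization and freedom from amputation at 3 and 12 months. It also includes a correlation between calcification and procedural complications. It contains no rate of procedure-related serious events. The Endpoints section provides independent reading for the angiographic data; the article describes nothing comparable for event causality.

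**The concern.** Two judgements decide whether an event counts: whether it is serious and whether the device caused it. The Endpoints wording ties the counted events to each site's usual practice, although the article has a common list in Table 3. The list then words two central complications of this treatment in the terms of the causality label that does not count.

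The study has one arm, so no comparator would reveal under-attribution. The Discussion reports that all 42 patients in the earlier investigation were free of serious device-related events at 30 days, so a figure near 100% is a plausible result here too. If it appears, the endpoint alone could not tell a reader whether few patients were seriously harmed or whether the harms were attributed to the procedure. Collecting safety data is a stated aim of the study, so this limits what its main safety number can support.

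**Working it through.** The article states no safety target, margin or test, so there is no figure of its own to reproduce. The check compares the sections and then sizes the effect under stated assumptions.

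**Following one event through the text**

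1. The Technique section says the rotating tip breaks atheroma or thrombus into particles that are aspirated at the same time. Distal embolism is a foreseeable result of that action, and the Background names it.
2. An embolus that causes acute limb ischemia meets Table 3 item c and is a serious event.
3. Under Follow-up it is assessed as related to device, procedure or neither.
4. If assessed as *device*, it counts against the primary safety endpoint. If assessed only as *procedure*, it is recorded but does not count.
5. The article gives no rule for choosing between the two at step 4.

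A thrombectomy or revision (item d) follows the same path. Perforation and vascular injury have no item of their own; they enter through the general seriousness criteria and then meet the same choice.

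**What one label is worth**

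Input: n = 60 (Study design). One patient is 1/60 = 1.7 percentage points.

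Assumption, since the documents give no rate: x of 60 patients have a serious event of this kind, and no other device-related event occurs. Intervals are two-sided 95% Clopper-Pearson.

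| x | Event rate, all counted | 95% CI | Freedom, all counted | Freedom, all labelled *procedure* |
|---|---|---|---|---|
| 1 | 1.7% | 0.04–8.9% | 98.3% | 100% |
| 3 | 5.0% | 1.0–13.9% | 95.0% | 100% |
| 6 | 10.0% | 3.8–20.5% | 90.0% | 100% |

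With nothing counted, 0/60 has an upper limit of 1 − 0.025^(1/60) = 6.0%. That limit bounds only the rate of events labelled *device*.

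**Chance of seeing no counted event**

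For a true rate r and a share s labelled *device*, the probability is (1 − r·s)^60. The values of r and s are assumptions.

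| r | s = 1 | s = 0.5 | s = 0 |
|---|---|---|---|
| 2% | 29.8% | 54.7% | 100% |
| 5% | 4.6% | 21.9% | 100% |
| 10% | 0.2% | 4.6% | 100% |

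At r = 5%, a clean result is unlikely if every event counts (0.95^60 = 4.6%). It is almost five times as likely if half are labelled *device* (0.975^60 = 21.9%).

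**The case against.** The case on the other side is substantial.

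- **Table 3 lists serious events and sets no causality rule.** Its reference to the procedure may only separate treatment complications from disease progression. A site may still label an embolus device-related, and the article does not say that the labels exclude each other. This stands: a reader might infer that embolization and revision are excluded by rule, but the text shows only that they can be.
- **A device-only endpoint suits a device study.** Treatment also involves access by different routes, angioplasty, stenting and hybrid steps, and a complication of these need not come from the device. This stands. The claim that device and procedure cannot be separated at all goes beyond the documents, and so does the claim that the primary endpoint has to be replaced.
- **The harms are partly visible elsewhere.** Revascularization and amputation at 3 months need no attribution, and all serious events are recorded. This stands in part: an embolus treated without target-vessel reintervention or amputation would appear in none of those endpoints.
- **The full protocol may define causality or provide adjudication.** This stands. A reader might infer that neither exists, or that the three sites in fact apply three different practices; the article shows neither. The finding rests on what it does fix, namely a device-only endpoint tied to site practice beside a separate *procedure* label.
- **A broader endpoint moves the attribution problem.** Someone must still separate *procedure* from *not related*. This stands, and is the reason for tabulating all-cause events as well.
- **A late change of the primary endpoint would be open to criticism.** Recruitment began in August 2022 and was expected to end in December 2023, with outcomes visible to investigators. This stands, and is the reason for adding an endpoint while leaving the primary one in place.

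**Conclusion.** The concern holds in a limited form. As written, the primary safety endpoint depends on site labelling, and serious atherectomy complications can fall outside it without any departure from the protocol. The secondary endpoints make up for this only in part. The data are not lost; the weakness lies in what the primary safety figure counts and therefore in what it can support.

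Each patient relabelled moves the result by 1.7 points. Over an assumed 1 to 6 affected patients, complete labelling as *procedure* would turn 98% to 90% freedom into 100%. These counts illustrate scale and predict nothing about the study. No stated success criterion would be overturned, because the article gives none. The consequence is for interpretation: freedom from SADE alone should not be presented as the safety of treatment with the device.

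**What to change.** 1. In the Endpoints section, replace the reference to site definition and normal reporting practice with Table 3 as the single definition of a serious adverse event at all three centers.
2. Keep device-only freedom from SADE to 90 days as the primary safety endpoint.
3. In a dated amendment before analysis, add a co-reported safety endpoint with its exact 95% CI: freedom from any Table 3 event judged related to the device or the procedure within 90 days.
4. Tabulate all-cause Table 3 events over the same 90 days beside both.

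With one event list and one window, the three patient counts are nested: device-only is at most device-or-procedure, which is at most all-cause. The gaps between them show how far the result depends on attribution, and safety conclusions should rest on all three.

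**Cost.** An amendment and two further summaries. No new visits, patients or data items are needed, since serious events and their relatedness are already recorded. The safety picture may look less favourable. The broader rate will also include access and adjunctive-treatment complications that the device did not cause, so it should be labelled as a rate for the whole procedure. Step 1 harmonizes seriousness only; attribution remains a judgement.
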